## Abstract

**Background::**

Hemorrhoidal disease (HD) is one of the commonest proctologic condition in the general population. Medical therapy for HD has not been formally confirmed due to the inconsistent of results. *Liang-Xue-Di-Huang* Decoction, a kind of ancient Chinese classical prescription, has been used to treat HD from the 19th century in China. However, clinical research of *Liang-Xue-Di-Huang* Decoction in the treatment of HD was lack. We designed this study to evaluate the efficacy and safety of *Liang-Xue-Di-Huang* Decoction in the treatment of HD.

**Methods/Design::**

A randomized, controlled, double blind, double-mimetic agent, and multicenter trial to evaluate the efficacy and safety of *Liang-Xue-Di-Huang* Decoction is proposed. HD patients (stage I, II, III) will be randomly assigned into experimental group or control group. HD patients will receive a 7-day treatments and a 7-day follow-up. The primary outcome measure is the Hemorrhoid Bleeding Score in 7 and 14 days. The Secondary outcome measures are Goligher prolapse score and quality-of-life score in 7 and 14 days.

**Discussion::**

This study will provide objective evidences to evaluate the efficacy and safety of *Liang-Xue-Di-Huang* Decoction in treatment of HD.

## Introduction

1

Hemorrhoidal disease (HD), one of the oldest and commonest proctologic condition in the general population, is more frequent in industrialized countries.^[1]^ Chronic bleeding is the main symptom of HD.^[2]^ The true prevalence of HD in the general population is unknown and probably different from country to country.^[3]^ In the United States, HD is the third most common outpatient gastrointestinal diagnosis, affecting between 20% and 50% of the population and resulting in 4 million emergency visits annually.^[4]^

Treatments for HD include medical therapies and surgery.^[5]^ Medical therapies for HD have not been formally studied where the results have been inconsistent.^[4]^ Increased fiber and fluid intake has been shown to improve symptoms of mild-to-moderate HD bleeding.^[6]^ However, the fiber is not recommended as primary treatment to severe bleeding.^[7]^ Another common medical prescription in patients with bleeding hemorrhoids is micronized purified flavonoid fraction. These drugs include diosmin, hesperidin, and cumarin. Each of these treatments has drawbacks, such as mild gastrointestinal disturbances.^[2]^

*Liang-Xue-Di-Huang* Decoction, a kind of Chinese herbal medicine, listed in Table 1, has been used for HD from the 19th century in China with good effects and few adverse events. In 2018, with the approval of the State Administration of Traditional Chinese Medicine of the People's Republic of China, *Liang-Xue-Di-Huang* Decoction has become one of the 100 classic prescriptions that can be used directly in clinical practice.^[8]^ However, it was still necessary to prove the efficacy and safety of this ancient Chinese classical prescription.

**Table 1 T1:**
[figure not shown]
Standard formulation of *Liang-Xue-Di-Huang* Decoction.

The aim of the present study is to determine: whether *Liang-Xue-Di-Huang* Decoction is useful for relieving HD bleeding, using a randomized, controlled, blind and multicenter trial among officially registered Chinese colorectal consultants, fellows and residents in China.

## Methods/design

2

### Design

2.1

This study is designed as a randomized, controlled, blind, and multicenter trial. Trained researchers introduce the trial to patients, give them information sheets and consent forms. All patients have to obtain “Ethics approval and consent to participate” section and give their written informed consents before enrolment. The study's flow chart is shown in Figure 1.

**Figure 1 F1:**
[figure not shown]
Study flow chart. The flow chart of enrolment, allocation, intervention and assessment.

### Ethics

2.2

The trial protocol is conducted in accordance with the Good Clinical Practice Guidelines and the Declaration of Helsinki (2008).^[9]^ Central ethical approval has been confirmed from the group leader's ethic committee of Affiliated Hospital of Nanjing University of Chinese Medicine (ref approval no. 2019NL-158-02) and 4 sub-centers ethical will comply with the group leader's ethics approval. Written informed consent will be obtained from each patient.

### Sample size

2.3

This is a pilot study. In the relevant literature, there are no previous studies utilizing the same evaluation method as the primary outcome to compare a classic prescription.

According to the literature search results, bleeding was used as the primary outcome measure for the treatment of HD by diosmin. It was estimated that *Liang-Xue-Di-Huang* Decoction treatment is not inferior to that of diosmin treatment.

According to the non-inferiority test sample size calculation formula, for a 2-sided significance level of 0.05, the standard deviation is 0.4, (α = 0.05, β = 0.2, δ = 0.15), the non-inferiority bound is 0.15 when the degree of grasp (1−β) = 80%, the sample size is calculated using the formula:

Considering a 10% loss to follow-up, it is expected that 240 patients in over 5 centers (1:1 division into experimental group and control group) will be enrolled and followed up for at least for 7 days.

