### Outcome measures

3.3

According to the latest treatment guidelines for HD,^[2]^ the primary outcome measure is the hemorrhoid bleeding score (Table 2). This score is a reliable and effective criterion for HD. The secondary outcome measure is Goligher prolapse score (Table 3) and quality-of-life score (Table 4).

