**Table 2 T2:**
[figure not shown]
Hemorrhoid bleeding score (Possible Score = 0–9).

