### Statistical analysis

3.10

Frequency, median, and mean ± standard deviation of the bleeding score, Goligher prolapse score and quality-of-life score will be used for descriptive statistics. The statistical analysis will be performed using SAS 9.4. *P* < .05 is considered statistically significant.

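### The SD of 0.4 and the margin of 0.15 carry no unit or source, and they do not support 80% power on a 0–9 bleeding score

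*Protocol article*

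**What the plan says.** Section 2.3 (Sample size) describes a non-inferiority calculation against diosmin "for a 2-sided significance level of 0.05" with 80% power. It gives the SD and the margin, its two scale-dependent inputs, as follows: "the standard deviation is 0.4, (α = 0.05, β = 0.2, δ = 0.15), the non-inferiority bound is 0.15". Allowing for 10% loss, it arrives at 240 patients, allocated 1:1. It attaches no unit to the SD or the margin and cites no source for either.

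Section 3.3 (Outcome measures) says that "the primary outcome measure is the hemorrhoid bleeding score". The caption of Table 2 gives the range: "Hemorrhoid bleeding score (Possible Score = 0–9". Section 3.10 (Statistical analysis) summarises the outcome on that scale: "Frequency, median, and mean ± standard deviation of the bleeding score". The visible text defines no responder and gives no expected response rate.

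Section 2.3 also remarks that "there are no previous studies utilizing the same evaluation method as the primary outcome". That sentence goes on to limit itself to comparisons involving a classic prescription.

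**The concern.** A power statement means something only if the SD and the margin are on the scale of the outcome to be compared. Here that outcome is a score with a 9-point range, while the inputs are 0.4 and 0.15. Both look very small for such a score, in a population that spans haemorrhoid stages I to III.

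For a fixed margin, power depends on the ratio of margin to SD. If the real SD is well above 0.4, the confidence interval for the difference in means will be too wide to exclude 0.15, and the trial may fail to show non-inferiority even when the two treatments are equivalent. Readers would meanwhile take the 80% as a property of the planned comparison.

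**Working it through.** **Inputs from the document:** SD 0.4; margin 0.15; two-sided α 0.05, so z = 1.960; power 80%, so z = 0.842; 10% loss; 240 patients in total (Section 2.3); score range 0–9 (Table 2 caption). **Assumed:** true difference 0, because none is stated.

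**1. Reproducing the plan's figure.**
n per arm = 2 × (1.960 + 0.842)² × 0.4² / 0.15² = 111.6, so 112 per arm and 224 in total. For 10% loss, dividing each arm by 0.90 gives 125 per arm (250), and multiplying by 1.10 gives 124 per arm (248). The stated 240 is 8 to 10 lower, which is a minor gap. With 240 × 0.90 / 2 = 108 evaluable per arm, power at SD 0.4 is 78.7%. So 240 is roughly what these two inputs produce.

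**2. Margin against the scale.**
0.15 / 9 = 1.7% of the range.

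**3. What SD 0.4 implies for whole-number scores (assumption).**
For two independent patients in one arm with scores X and X′, Var = ½E(X − X′)². Whole-number scores that differ do so by at least 1, so Var ≥ ½(1 − Σp²), where p are the proportions at each score. With Var = 0.16, Σp² ≥ 0.68. Let m be the largest p. Since Σp² ≤ m, m is at least 0.68. Since Σp² ≤ m² + (1 − m)², it follows that m² − m + 0.16 ≥ 0, so m ≥ 0.8. At least 80% of the arm must have the same score.

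**4. Power for a margin of 0.15 with 108 per arm.**
Power = Φ(0.15 / (SD × √(2/108)) − 1.960), where √(2/108) = 0.1361. This step does not need whole-number scoring.

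| SD (values above 0.4 are assumptions) | Power |
|---|---|
| 0.4 | 79% |
| 0.6 | 45% |
| 0.8 | 28% |
| 1.0 | 20% |
| 1.5 | 11% |
| 2.0 | 8% |

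The largest SD that gives 80% is 0.15 / (2.802 × 0.1361) = 0.393, so the plan has no slack. The half-width of the 95% interval is 1.960 × 0.1361 × SD = 0.267 × SD. It exceeds 0.15 once the SD passes 0.15 / 0.267 = 0.56; beyond that, even an observed difference of exactly zero would not exclude the margin.

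**5. Margin that 108 per arm supports at 80% power.**
2.802 × 0.1361 × SD = 0.381 × SD, for example 0.38 points at SD 1.0 and 0.57 points at SD 1.5.

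**The case against.** The best defence is a floor effect. If 80% of an arm scores 0 after treatment and the other 20% scores exactly 1, the SD is √(0.8 × 0.2) = 0.4. The documents neither support nor exclude this, so SD 0.4 is not impossible. It is fragile, though: if that 20% scores 2, the SD doubles to 0.8 and power is 28%. Baseline adjustment helps only with a very strong correlation. Bringing a raw SD of 1.0 down to 0.4 needs √(1 − 0.16) = 0.92.

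The sample-size formula and the body of Table 2 are also not visible, and a condensed article may leave a source to the full protocol. That limits what can be said about where the figures came from. It does not change the fact that the inputs, the power and the outcome are all stated here and do not visibly fit together.

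A reader might infer three stronger things that the text does not carry:

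- **That the calculation was really for a proportion.** An 80% response rate has SD 0.4, and 0.15 could be 15 percentage points. But Section 2.3 calls 0.4 a standard deviation, and no rate is stated. A 20% rate fits equally well. The matching 112 per arm is an algebraic identity, not independent evidence. This is a possible explanation only.
- **That the protocol admits it had no data on the score.** The remark "there are no previous studies utilizing the same evaluation method as the primary outcome" concerns comparisons of a classic prescription, and the next paragraph refers to literature on diosmin with a bleeding outcome. What stands is that no source is cited for 0.4 or 0.15.
- **That the trial is nearly certain to be inconclusive.** That describes SDs of about 1.5 or more. At SD 0.6, power is 45%. The score's SD is not in the documents.

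**Conclusion.** The point holds in a limited form: the 80% power in Section 2.3 is not supported for the primary outcome. The SD and margin have no stated unit or source, the margin is 1.7% of the score's range, and under whole-number scoring the SD needs at least 80% of an arm on one value. With the 0.15 margin, power drops from 79% at SD 0.4 to 20% at SD 1.0 and 8% at SD 2.0.

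This rests on 108 evaluable patients per arm, a true difference of zero, a comparison of means on the raw score, and assumed SDs above 0.4. The true power is unknown. The conclusion is that 80% is unsubstantiated and falls quickly if the SD exceeds 0.4, not that any one lower figure is correct. Because the power statement underlies the primary non-inferiority comparison, it should be corrected before unblinding.

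**What to change.** In Section 2.3:

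1. State the unit and source of 0.4 and 0.15.
2. Restate the SD, and a margin justified on clinical grounds, in bleeding-score points.
3. Check the SD on blinded pooled data.
4. Before unblinding, replace the 80% with the power that 240 patients (about 108 evaluable per arm) give for that margin.

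For reference, 108 per arm gives 80% power only for a margin of about 0.38 SD. The margin should not be chosen to meet that figure.

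Keep the bleeding score as the primary outcome. Switching to a responder endpoint would replace the stated outcome to suit a guessed calculation. No additional patients are needed.

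The cost is a rewritten sample-size paragraph, a short amendment and a blinded variance check. The downside is that the reported power will probably be less favourable than 80%.

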### Recruitment

2.4

A total of 240 participants who fulfill the screening criteria will be invited to participate to this RCT at 5 hospitals in China:

1.Group leader, Affiliated Hospital of Nanjing University of Chinese Medicine, will recruit 64 participants through posters,2.Sub-center, Changzhou Hospital of Traditional Chinese Medicine, will recruit 60 participants through posters,3.Sub-center, Suzhou Hospital of Traditional Chinese Medicine, will recruit 60 participants through posters,4.Sub-center, Xuyi Hospital of Traditional Chinese Medicine, will recruit 28 participants through posters,5.Sub-center, Wujin Hospital of Traditional Chinese Medicine, will recruit 28 participants through posters.

Each-center research assistant will screen participants and obtain their written informed consent. Then, participants will be randomly allocated into either experimental group or control group. The schedule of enrolment, intervention, and assessments is detailed in Figure 1.

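### With the inputs as printed, 240 patients fall 7 to 9 short of 80% power at 10% loss; power is about 79%, and the gap may come from a rounded SD (minor)

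*Protocol article*

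**What the plan says.** Section 2.3 (Sample size) of the protocol article frames the aim as showing that the decoction "treatment is not inferior to that of diosmin treatment". It gives the inputs in the text: "for a 2-sided significance level of 0.05", "the standard deviation is 0.4", "the non-inferiority bound is 0.15", with β = 0.2, that is 80% power. Allocation is a "1:1 division into experimental group and control group". The enrolment target follows: "Considering a 10% loss to follow-up, it is expected that 240 patients in over 5 centers".

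Section 2.4 (Recruitment) repeats the target: "A total of 240 participants who fulfill the screening criteria will be invited". Its five centre quotas, 64 + 60 + 60 + 28 + 28, also add to 240, so the number is not a typing slip.

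The formula is not visible in the text at hand, which is not held against the plan. The visible text gives neither the sample size before the loss allowance nor a true difference between the arms.

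**The concern.** The section makes two promises with one number: 80% power, and room for 10% loss. Every input needed to check them is printed except the true difference. If the inputs give an enrolment above 240, one of the two promises has to give way.

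What is at stake is how accurately the design is described. A non-inferiority result turns on the width of the confidence interval against a fixed margin, so readers will take the quoted power as the chance of success if the two treatments are equally effective. That figure should follow from the stated inputs.

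**Working it through.** **Inputs, all from section 2.3 unless marked**

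- Alpha: 0.05 two-sided, so 0.025 on the side that matters for non-inferiority; z = 1.960
- Power: 80%; z = 0.842
- SD: 0.4
- Margin: 0.15 (δ = 0.15 is read as the same quantity)
- Allocation 1:1; loss 10%; enrolment 240
- True difference: 0 (assumption; not stated)

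**Step 1. Evaluable patients needed**

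n per arm = 2 × (1.960 + 0.842)² × SD² / margin² = 2 × 7.849 × 0.16 / 0.0225 = 111.6, rounded up to 112. The total is 224 evaluable.

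**Step 2. Allowance for 10% loss**

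- Dividing by the retained share: 224 / 0.9 = 248.9, so 249 enrolled.
- Multiplying by 1.1, which is common but slightly too small: 224 × 1.1 = 246.4, so 247 enrolled.
- Without rounding n first, the two routes give 248.1 and 245.6.

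All four results lie above 240. With rounded n, the shortfall is 7 (247 − 240) to 9 (249 − 240) patients.

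**Step 3. What 240 delivers**

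- At 10% loss: 240 × 0.9 = 216 evaluable, 108 per arm. The standard error is 0.4 × √(2/108) = 0.05443, and 0.15 / 0.05443 = 2.756. Power = Φ(2.756 − 1.960) = 78.7%. The t distribution gives 78.3%.
- With no loss: 120 per arm gives 82.8% (82.5% by t).
- Loss that 240 can absorb and still leave 224: 1 − 224/240 = 6.7%.

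At 10% loss, 224 − 216 = 8 evaluable patients are missing. That is 3.6% of the 224 required.

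**Step 4. Can another reading give 240?**

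- *One-sided alpha 0.05.* n per arm = 2 × (1.645 + 0.842)² × 0.16 / 0.0225 = 87.9, so 88; 176 / 0.9 = 195.6, so 196 enrolled. This does not match 240, although 108 per arm would then have 86.7% power. The text states a two-sided level.
- *An SD that prints as 0.4 (assumption).* SD 0.393: n = 2 × 7.849 × 0.393² / 0.0225 = 107.8, so 108 per arm, and 216 / 0.9 = 240 exactly. SD 0.395: n = 108.9, so 109 per arm, and 218 × 1.1 = 239.8, which rounds to 240. A slightly smaller, unrounded SD can therefore produce the protocol's number.

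**Step 5. Optional gain from baseline adjustment (assumed correlations)**

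Adjusting for a baseline value with correlation r reduces the SD to 0.4 × √(1 − r²). At 108 per arm:

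| r | SD | Power, normal | Power, t |
|---|---|---|---|
| 0.20 | 0.392 | 80.3% | 79.95% |
| 0.25 | 0.387 | 81.2% | 80.9% |
| 0.30 | 0.382 | 82.3% | 82.0% |

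**The case against.** The case for leaving the sentence alone is that the discrepancy is of rounding size. By the cruder inflation, 247 is 2.9% above 240; by the stricter one, 249 is 3.75% above. Power misses by 1.3 points, or 1.7 by t, in what the article itself describes as a pilot study. Treatment lasts 7 days with 7 days of follow-up, so loss may well stay under 6.7%. The SD is printed to one decimal, and a value of 0.393 to 0.395 recovers 240.

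Most of this stands, and it limits the point. A reader might infer that 240 cannot be derived under any reading, or that the trial is materially underpowered. The documents support neither. The first is answered by the rounding of the SD; the second by the size of the gap. It also cannot be said that 80% power is unattainable, because 240 reaches it whenever loss is 6.7% or less.

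What does not stand is that the sentence is therefore correct. The SD rounding is an assumption that the article does not confirm. On the figures as printed, 80% power and a 10% loss allowance do not hold together. The 1.1 multiplier does not help either: 247 less 10% leaves about 222, still under 224.

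**Conclusion.** The point holds as a minor correction to the stated justification. With two-sided alpha 0.05, SD exactly 0.4, margin 0.15 and 80% power, 224 evaluable and 247 to 249 enrolled patients are needed. The planned 240 gives about 79% power (78.7% normal, 78.3% t) at 10% loss.

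This rests on a true difference of zero, the usual choice but not a stated one, and on the standard two-mean non-inferiority formula. If the decoction were slightly worse than diosmin, power would be lower: a true disadvantage of 0.01 gives 73.0% at 108 per arm. If the SD used was about 0.393 to 0.395, the discrepancy disappears and only the reporting needs completing.

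**What to change.** Keep 240 and change one sentence in section 2.3. Any one of these is enough:

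- State about 79% power with 10% loss.
- State 80% power with up to 6.7% loss.
- If a less rounded SD was used, print it with the number needed per arm before the loss allowance, so that 240 can be followed.

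In each case, state that the true difference is taken as zero, if that is what was assumed.

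Optionally, if the bleeding score is recorded at baseline, adjust the primary comparison for it. A baseline to day-7 correlation of about 0.25 or more would bring power above 80% at 10% loss by either calculation. That correlation is assumed. Section 2.5 (Randomization) mentions a baseline assessment before allocation, but the visible text does not say that it includes the bleeding score. The correction should therefore rest on the restated figure and not on this option.

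The cost is one sentence. Enrolment and centre quotas stay as they are.

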### Recruitment

2.4

A total of 240 participants who fulfill the screening criteria will be invited to participate to this RCT at 5 hospitals in China:

1.Group leader, Affiliated Hospital of Nanjing University of Chinese Medicine, will recruit 64 participants through posters,2.Sub-center, Changzhou Hospital of Traditional Chinese Medicine, will recruit 60 participants through posters,3.Sub-center, Suzhou Hospital of Traditional Chinese Medicine, will recruit 60 participants through posters,4.Sub-center, Xuyi Hospital of Traditional Chinese Medicine, will recruit 28 participants through posters,5.Sub-center, Wujin Hospital of Traditional Chinese Medicine, will recruit 28 participants through posters.

Each-center research assistant will screen participants and obtain their written informed consent. Then, participants will be randomly allocated into either experimental group or control group. The schedule of enrolment, intervention, and assessments is detailed in Figure 1.

### Randomization

2.5

With the help of SAS 9.4 statistical software, a random sequence will be produced by block randomization. The randomization procedure will be conducted by research assistants using an online computerized randomization system (https://sci.medroad.cn/). Before the beginning of treatment, participants were told that they have the same probability of being assigned to experimental group or control group. After the participants have completed the screening process and baseline assessment, they will be randomly assigned to experimental group or control group in a 1:1 ratio. The group numbers will be kept by an independent administrator who will not directly participate in the recruitment or follow-up of any participant.

### Blinding

2.6

This trial is a double-blind design in which neither the patients nor the investigators (including statisticians) will be aware of their treatments during the trial period. Each hospital receives an emergency letter, which will be preserved until the end of the trial. Code-breaking should occur only in the case of serious adverse events happen, with the permission of the person in charge of the research center. A report should be submitted to the leader of the trial within 24 hours.

### Inclusion criteria

2.7

Participants who meet all of the following criteria can be included:

1.Comply with hemorrhoids standards diagnosis (stage I, II, III)^[2]^;Comply with “Traditional Chinese Medicine disease and syndrome, diagnosis and curative effect standard” damp-heat syndrome: bleeding hemorrhoids, bright red blood^[10]^;2.Participant signed the informed consent form;3.Participant agreed to avoid other hemorrhoids medications during the trial.

